### Interventions

To reflect the consensus regarding usual practice for administering corticosteroid injection for CTS in primary care, participants randomised to injection will receive one injection of 20 mg of Depo-Medrone (from 40 mg/ml) via a disposable needle (23 or 25G) and syringe. This will be inserted at the wrist to infiltrate the carpal tunnel. A sterile ‘no-touch’ technique will be used and the addition of local anaesthetic is not permitted. The patient will sit with the hand placed palm upwards in a neutral or slightly extended wrist position. The skin is cleaned according to local policy and the needle inserted between the proximal and distal skin creases at the wrist, preferably on the ulnar side of the Palmaris longus which lies over the median nerve. The needle is angled at 45 degrees distally to enter the carpal tunnel. Occasionally, due to anatomical variations, e.g. large superficial veins, the injection may be given on the radial side of the Palmaris longus. Injections into the palm of the hand are not permitted as there are rare reports of ischaemic necrosis of the fingertips presumably due to the needle penetrating the palmar arterial arch. Participants will be advised to wait for 30 min following injection and to rest the injected arm for 48 h. They will be given two Arthritis Research UK patient leaflets: “Carpal tunnel syndrome” and “Local corticosteroid injections”. No other additional types of therapy are advised during the 6 week treatment period except for simple analgesia prescribed by the treating clinician or bought over the counter (e.g. paracetamol, NSAIDS), information about which will be captured via the 6 week questionnaire.

Participants randomised to night splints will receive a splint to wear at night for 6 weeks. The splint immobilizes the wrist in a neutral or slightly extended position (20 degrees from neutral) in order to avoid movement of the wrist, which increases carpal tunnel pressure [20]. The Promedics® Beta Wrist Brace (with CE Marking) is designed to avoid restriction at metacarpophalangeal joints and thumb, and the binding will ensure comfort to enhance adherence to splint wearing. Each splint will be fitted according to the size of the participant’s hand and arm using standard splints of differing sizes. The wrist angle will be in neutral position (between 0 and 20 degrees) to reduce carpal tunnel pressures. No other types of therapy will be permitted during the 6 weeks, except simple analgesia prescribed by the treating clinician or bought over the counter (e.g. paracetamol, NSAIDS), which will be captured in the 6 week questionnaire.

Participants will be shown how to fit and remove the wrist splint according to a standardised trial protocol. Adherence will be encouraged and reinforced by verbal instruction from the clinician on how and when to use the splint and this will be supported by written information, detailing care, fitting and use of the splint. Participants will be instructed to perform gentle range-of-motion exercises when removing the splint to prevent stiffness. They will also be given two Arthritis Research UK patient leaflets: “Carpal tunnel syndrome” and “Splints for arthritis of the hand and wrist”.

For participants with bilateral CTS, the non-study hand will be treated according to normal clinical protocols in use at the research site.

### Outcome measures and endpoints

The primary endpoint will be at 6 weeks post randomisation and secondary endpoints will be at 6, 12 and 24 months post randomisation. Table 2 explains which outcomes are collected at the different time-points. The primary outcome measure will be the overall score of symptom severity and limitations in hand function as assessed by the BCTQ [21] which has previously been shown to be highly reproducible, internally consistent, valid, and responsive to clinical change in CTS patients [22, 23]. The BCTQ is a disease specific questionnaire referring to a typical 24 h period in the last 2 weeks. It consists of two subscales: symptom severity scale (SSS: 11 items) and function status scale (FSS: 8 items), both scored on 1–5 point scales, with final scores for each dimension calculated as a mean score between 1 and 5. The overall score is calculated as the mean of all 19 items. Higher scores correlate with more severe symptoms and functional impairment.

Secondary outcome measures include; BCTQ symptom severity and function status subscales [21], hand-wrist symptom intensity (0–10 numerical rating scale), interrupted sleep, [24] self-reported adherence to splinting where indicated (Likert scale modified from previous research [25]), patients’ perceived benefit and satisfaction with treatment (Likert scale modified from previous research) [25], impact of CTS on work and other activities (including work absence and reduction in work performance measured by a 0–10 rating scale), referral for surgery, surgery, general health (EuroQoL EQ-5D-5L) [26], quality adjusted life years, health care utilisation and patient incurred costs, and use of co-interventions such as supplements and analgesia. Participants’ expectations regarding treatment response [25] and presence of bilateral CTS symptoms will be explored as potential effect modifiers.

**Table 2 Tab2:** Outcome measures and data collection time points

Baseline measures	Description	Baseline	6 week follow-up	6 month follow-up	12 month follow-up	24 month follow-up
Demographics	gender, date of birth	✓	✓	✓	✓	✓
Previous CTS episodes	number of episodes and treatments	✓				
Current CTS episode	location and duration	✓				
Participant preference and expectations for treatment	Likert Scale adapted from previous research	✓				
General Health	Self-reported health and comorbidities	✓				
Primary outcome measure						
Hand/wrist pain and function	Boston CTS questionnaire	✓	✓	✓	✓	✓
Secondary outcome measures						
Hand/wrist pain intensity	NRS (0–10) over last 24 h	✓	✓	✓	✓	✓
Interrupted Sleep	Estimation of interruption to sleep scale	✓	✓	✓		
Adherence with splinting	Scales adapted from previous research		✓			
Other Treatments received	Self-reported referral to surgery and prescribed analgesia		✓	✓	✓	✓
Satisfaction and experience	Likert scales adapted from previous research		✓			
Health economic outcomes						
Health related quality of life	EuroQoL:EQ-5D-5L	✓	✓	✓	✓	✓
Employment	Current employment status and employer support	✓	✓	✓	✓	✓
Performance at work	How performance at work is affected NRS 0-10	✓	✓	✓	✓	✓
Work absence	Self-report days absent from work	✓	✓	✓	✓	✓
Healthcare utilisation	Primary care consultations			✓	✓	✓
	Secondary care contacts including investigations					
	Prescribed medications					
	Use of private healthcare					
Patient-incurred costs and use of co-interventions	Over-the-counter medications or interventions			✓	✓	✓

Schedule of events

### Adverse events

Although Depo-Medrone is not specifically licensed for use in CTS, it has been widely used for many years in standard practice in both primary and secondary care and has a very well established and understood safety profile [27–29]. It is being used within the injection protocol in accordance with the guidance given in the BNF [28] for local inflammation in soft tissues and expert opinion provided in Map of Medicine [27] regarding the use of corticosteroid for CTS. The incidence of adverse predictable undesirable side-effects associated with the use of corticosteroids correlates with the relative potency of the drug, dosage, and timing of administration and duration of treatment, and therefore based on the dosage to be used in this study, there is no requirement within this study to record non-serious adverse events beyond normal clinical practice. Where a Serious Adverse Event (SAE) or Suspected Unexpected Serious Adverse Reaction (SUSAR) occurs, reporting procedures are in place that are in accordance with good clinical practice guidance and the requirements specified by the MHRA. All SAEs will be considered by the external monitoring committees.

### Data collection methods

All participants enrolled in the study will be asked to complete a paper questionnaire at the baseline clinical appointment and again at 6 weeks, 6, 12 and 24 months when a questionnaire will be posted to them. Questionnaires will capture data on all outcome measures. If the questionnaire is not returned within 2 weeks of initial mailing, a reminder will be sent (text message, e-mail, or telephone call). If the questionnaire is still not returned, a second follow-up questionnaire will be sent 4 weeks later. For non-responders, minimum data collection (MDC) to capture the primary outcome measures will be undertaken by a research nurse by telephone at 2 weeks after mailing of the second questionnaire. Where a participant is not able to be contacted by telephone within three working days, a postal MDC questionnaire will be sent. Patients who do not respond or are not contacted by telephone will still be sent subsequent questionnaires at further follow-up time points unless they request not to.

The flow events as participants proceed through the trial is outlined in (Fig. 1) and the the timing of key events outlined in Table 3.

**Fig. 1 Fig1:**
[figure not shown]
Flow of participants through the trial

**Table 3 Tab3:** Participant timeline

Visits	Screening	Baseline and intervention Day 0	6 week follow-up	6 month follow-up	12 month follow-up	24 month follow-up
Diagnosis	✓					
Eligibility Screening	✓					
*GP pathway only:* Written Informed Consent for contact by Keele RN and completion of Consent to Contact Fax Form	✓					
*GP pathway only:* Keele RN telephone call to potential participant	✓					
*GP pathway only:* Confirmation of Eligibility and Randomisation		✓				
Informed consent by authorised local Investigator		✓				
Participant Baseline Data self-report Questionnaires		✓				
Web randomisation		✓				
Administration of study intervention		✓				
Participant self-report follow up Questionnaires			✓	✓	✓	✓

### Statistical analysis

#### Primary analysis at 6 weeks

Baseline characteristics will be summarized for the two treatment groups using appropriate descriptive statistics. The primary analysis will be conducted blind to treatment allocation and will be analysed on intention to treat (ITT) approach with all randomised participants retaining their original randomised group. Multiple imputation using chain equations [30] will be used to impute missing data. Sensitivity analyses will be performed to compare ITT results to those based on complete-case analysis.

Multiple linear regression will be used to obtain the mean estimates and 95 % confidence intervals for the difference in the BCTQ overall score at 6 weeks between the treatment groups adjusting for age at recruitment, sex, duration of symptoms, and index score at baseline.

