### Recruitment, screening process and enrolment

Participants will be recruited from up to 50 sites including; GP practices, primary-secondary care musculoskeletal interface clinics throughout the UK. Research sites will have received NHS permission and trial specific training covering the interventions and trial administrative procedures (Additional file 1).

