### Randomisation

Prior to randomisation all participants will complete the baseline questionnaire, which includes questions regarding sociodemographic characteristics, outcome measures and potential prognostic factors. Participants will be randomised by the local clinician, in a 1:1 ratio via a remote web based randomisation system, which ensures the allocation sequence is concealed. The randomisation sequence is based on computer generated, random permuted blocks of sizes 2 and 4 and will be blocked by research site. Following completion of randomisation patients will be given a patient card detailing their treatment allocation, which they are asked to carry at all times during the first 6 weeks and to present it to medical staff should they be admitted to hospital during this time on the study.

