#### Secondary analyses (outcomes up to 6 months)

Using similar methods described for the primary analysis, the effect of treatment will be estimated over the medium term (6 months post-randomisation) as measured by the BCTQ overall score, and also for the secondary outcome measures listed above recorded at 6 weeks and 6 months.

Per protocol analyses, based on self-report adherence to night splinting and use of a single injection, will be carried out. No interim analyses are planned.

Potential effect modifiers, i.e. participants’ expectations regarding treatment response and presence of bilateral CTS, will be explored through adding moderator*treatment interactions to the models estimating the primary outcome of symptom severity and function (acknowledging that interpretation of *p*-values will be placed in context of anticipated low power as well as the exploratory nature of the tests), and describing effects of treatment for subgroups of patients defined based on modifying variables.

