### Sample size and calculation

Although previous studies using the BCTQ have provided information on the minimal important within-group change (0.23 points) there is limited evidence to underpin the definition of a minimum clinical important difference between the expected effects of injections versus night splinting for the primary outcome measure. Previously published RCTs have either examined the effectiveness of injection or night-splinting in patients with CTS, but very few have compared the two treatments. As both the treatments in this trial are active, we would expect a smaller difference between the treatment groups than if an active were compared to a control group, where a minimum of a 20 % difference might be expected. Hence, in order to detect a 15 % greater improvement, as measured by the BCTQ from an expected baseline value of approximately 2.9 points (scale 1–5, SD 1.0) [18, 31–33] in the injection group compared to night-splinting (i.e. a 0.9-point (30 %) reduction in the injection group versus a 0.45-point (15 %) reduction in the night splinting group, with pooled SD of 1.0, SMD 0.45), we would need complete data for 200 patients (100 in each treatment group) given approximately 90 % power and 5 % two-tailed significance. By adopting an initial sample size that would take account of 15 % loss of data (which we achieved in previous similar studies), we would need to recruit 120 participants per treatment group, 240 patients altogether. Through routine, 6-monthly examination of the follow-up rates, as part of the reporting for the Trial Steering and Data Monitoring Committees, we will be able to examine the deviation of the observed attrition rate from the expected 15 % factored into the sample size calculation.

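### Randomisation is blocked by site but the primary model omits site: if sites differ in mean outcome, the interval is slightly too wide (0 to about 5% for an assumed ICC of 0 to 0.10)

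*Protocol article*

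**What the plan says.** Under Randomisation, the article describes 1:1 allocation using "random permuted blocks of sizes 2 and 4 and will be blocked by research site". I read this as a separate blocked sequence for each site, so site is a stratification factor, and it is the only one stated. Under Recruitment, screening process and enrolment: "Participants will be recruited from up to 50 sites". These are a mixture of general practices and musculoskeletal interface clinics.

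Under Primary analysis at 6 weeks: "Multiple linear regression will be used to obtain the mean estimates and 95 % confidence intervals" for the treatment difference, "adjusting for age at recruitment, sex, duration of symptoms, and index score at baseline". Site is not in that list, and no random effect or other allowance for site is mentioned. Under Secondary analyses (outcomes up to 6 months), the approach carries over: "Using similar methods described for the primary analysis". The Sample size and calculation section makes no allowance for site either.

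**The concern.** Balancing allocation within site removes most of the between-site variation from the treatment contrast. A model without site still counts that variation as residual noise. If sites differ in mean outcome, the reported standard error is larger than the true sampling error, so the confidence interval is wider than the design has earned and the test rejects less often than 5% under the null.

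Some between-site variation is plausible. The Discussion says the interface services take referrals from practitioners who do not themselves inject these patients, so the route into the trial differs by type of site. That gives a reason to expect variation but does not quantify it. What is at stake is the accuracy of the reported precision. The treatment estimate itself hardly changes.

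**Working it through.** **Inputs from the article.** Difference 0.45 points, SD 1.0; 100 complete per arm; two-sided 5%; 240 recruited with 15% loss; up to 50 sites; blocks of 2 and 4. **Assumed:** between-site ICC of the 6-week score after adjustment, 0 to 0.10. The article gives no value.

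**1. The plan's own figure.** The article's basis is "complete data for 200 patients (100 in each treatment group) given approximately 90 % power and 5 % two-tailed significance". SE = √(2/100) = 0.1414. Power = Φ(0.45/0.1414 − 1.96) = Φ(1.222) = 88.9%, which agrees with the stated approximate 90%. Exactly 90% would need 104 per arm.

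**2. Site size.** With all 50 sites in use, 240/50 = 4.8 randomised per site. Analysed: 240 × 0.85 = 204, and 204/50 is about 4.1 per site.

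**3. Formula.** With total variance 1 and balance within site, the true SE is about 0.1414 × √(1 − ICC), while the model without site reports about 0.1414. Hence:
- interval ratio = 1/√(1 − ICC)
- actual type I error = 2[1 − Φ(1.96/√(1 − ICC))]
- power omitting site = Φ((3.182 − 1.96)/√(1 − ICC))
- power with site = Φ(3.182/√(1 − ICC) − 1.96)

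| Assumed ICC | Interval too wide by | Type I error, site omitted | Power, site omitted | Power, site modelled | Points forgone |
|---|---|---|---|---|---|
| 0 | 0% | 5.0% | 88.91% | 88.91% | 0 |
| 0.02 | 1.0% | 4.8% | 89.15% | 89.51% | 0.36 |
| 0.05 | 2.6% | 4.4% | 89.50% | 90.40% | 0.90 |
| 0.10 | 5.4% | 3.9% | 90.11% | 91.84% | 1.73 |

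**4. Simulation with the ICC treated as known** (2,000 runs per scenario, 25 or 50 unequal sites, blocks of 2 and 4, 15% loss, no covariates). With 50 sites, a true difference of 0.45 and ICC 0.10, the mean 95% half-width was 0.2758 without site and 0.2646 with a random intercept, a ratio of 1.042. At ICC 0.05 it was 0.2750 against 0.2697, a ratio of 1.020. The gain is a little below the formula, as expected with incomplete small blocks and dropout. The empirical SD of the estimate at ICC 0.10 was 0.1335 against 0.1332, so only the reported precision changes. Null rejection rates from these runs carry a simulation error of √(0.05 × 0.95/2000), about 0.5 points. At 50 sites and ICC 0.10 they were 4.9% and 5.5%, which is too coarse to fix the level.

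**5. Simulation with the site variance estimated by REML** (same design). At ICC 0.10, type I error was about 4.0% without site and 4.8% with it, the SE went from 0.140 to 0.134, and power from about 91% to 92.5%. At ICC 0.05 the gain was about 1 point of power. At 0 to 0.02 it was about nil, with essentially no penalty for the random intercept.

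**6. Fixed or random site effects.** From the simulation in step 4 with 50 sites, power (simulation error about 0.7 points) was:
- ICC 0.05: 89.9% omitting site, 91.0% with a random intercept, 88.6% with fixed site effects.
- ICC 0: 89.6% omitting site, 86.2% with fixed site effects.

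**7. Treatment effect varying by site.** A further simulation (6,000 runs, null average effect, sites treated as a random sample) put the site variation in the injection arm only. Without site in the model, type I error at arm-specific ICCs of 0.02, 0.05 and 0.10 was 5.7%, 7.4% and 8.7% with 25 sites, and 5.7%, 5.7% and 6.7% with 50 sites. The direction reverses.

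**The case against.** The strongest objection is that the harm depends on a number the article does not give. At ICC 0 nothing is lost, and at 0.02 the loss is trivial. That stands, so the point must be conditional.

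Second, the model already adjusts for baseline score, symptom duration, age and sex, which may absorb part of the case-mix differences between sites. This also stands, but it does not settle the matter: adjustment lowers the residual variance as well, so the share due to site could fall or rise.

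Third, sites are small and the site variance will be poorly estimated. That is true, but the REML simulation shows most of the small gain survives and that little is lost if sites do not differ.

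Fourth, Timing of analysis refers to an agreed analysis plan that is not shown and may include site. If it does, the point is resolved. The article, however, does not leave the model open: it gives an explicit covariate list without the factor used in the randomisation. The contents of the imputation model are ordinary analysis-plan detail, and their absence from the article is not a fault.

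A reader might also infer that differences in injectors between sites make the interval too wide. The reasoning does not support this. Injector skill acts on one arm only, so it is variation in the treatment effect; as step 7 shows, the standard error can then be too small, and a random intercept alone does not model that.

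**Conclusion.** The mismatch between design and analysis is in the text, and the direction of the error follows if site differences are shared by both arms. For an assumed ICC of 0 to 0.10, the interval is 0 to about 5% too wide, type I error falls from 5% to about 4%, and 0 to about 2 points of power are forgone. The calculations ignore baseline covariates and assume a treatment effect that is constant across sites.

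A reader might go further and conclude that the trial is underpowered or that its primary result would be unsafe. Neither follows. Power without site does not fall below the 88.9% that the planned numbers give, and under shared site differences the error is conservative, so it does not raise the false-positive rate. This is a modest point, worth correcting because the correction costs so little.

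**What to change.** State that the primary model, and the secondary models for continuous outcomes, include a random intercept for research site in addition to the four listed covariates. Do not use fixed site effects, which can lose power at about 4 to 5 participants per site. Carry site into the multiple-imputation model where feasible, so that the imputation and analysis models agree. If the investigators prefer to leave site out, they should give the reason.

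The cost is a line of analysis wording and slightly more analysis work. Site must already be known for the randomisation to run, and nothing changes for participants or sites. The one technical drawback is a site variance that is imprecisely estimated when sites are small.

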#### Secondary analyses (outcomes up to 6 months)

Using similar methods described for the primary analysis, the effect of treatment will be estimated over the medium term (6 months post-randomisation) as measured by the BCTQ overall score, and also for the secondary outcome measures listed above recorded at 6 weeks and 6 months.

Per protocol analyses, based on self-report adherence to night splinting and use of a single injection, will be carried out. No interim analyses are planned.

Potential effect modifiers, i.e. participants’ expectations regarding treatment response and presence of bilateral CTS, will be explored through adding moderator*treatment interactions to the models estimating the primary outcome of symptom severity and function (acknowledging that interpretation of *p*-values will be placed in context of anticipated low power as well as the exploratory nature of the tests), and describing effects of treatment for subgroups of patients defined based on modifying variables.

